## Abstract

**Background:**

Haemodialysis (HD) is critically dependent on the availability of adequate access to the systemic circulation, ideally via a native arteriovenous fistula (AVF). The Primary failure rate of an AVF ranges between 20–54%, due to thrombosis or failure of maturation. There remains limited evidence for the use of anti-platelet agents and uncertainty as to choice of agent(s) for the prevention of AVF thrombosis. We present the study protocol for a randomised, double-blind, placebo-controlled, clinical trial examining whether the use of the anti-platelet agents, aspirin and omega-3 fatty acids, either alone or in combination, will effectively reduce the risk of early thrombosis in de novo AVF.

**Methods/Design:**

The study population is adult patients with stage IV or V chronic kidney disease (CKD) currently on HD or where HD is planned to start within 6 months in whom a planned upper or lower arm AVF is to be the primary HD access. Using a factorial-design trial, patients will be randomised to aspirin or matching placebo, and also to omega-3 fatty acids or matching placebo, resulting in four treatment groups (aspirin placebo/omega-3 fatty acid placebo, aspirin/omega-3 fatty acid placebo, aspirin placebo/omega-3 fatty acid, aspirin/omega-3 fatty acid). Randomisation will be achieved using a dynamic balancing method over the two stratification factors of study site and upper versus lower arm AVF. The medication will be commenced pre-operatively and continued for 3 months post surgery. The primary outcome is patency of the AVF at three months after randomisation. Secondary outcome measures will include functional patency at six and twelve months, primary patency time, secondary (assisted) patency time, and adverse events, particularly bleeding.

**Discussion:**

This multicentre Australian and New Zealand study has been designed to determine whether the outcome of surgery to create de novo AVF can be improved by the use of aspirin and/or omega-3 fatty acids. Recently a placebo-controlled trial has shown that clopidogrel is effective in safely preventing primary AVF thrombosis, but ineffective at increasing functional patency. Our study presents significant differences in the anti-platelet agents used, the study design, and surgical and patient demographics that should contribute further evidence regarding the efficacy of anti-platelet agents.

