Therefore, while the clinical imperative is to establish AVF in as many patients as possible, primary failure because of early thrombosis and failure of maturation are the major impediments to clinical success[8]. Reports in the literature from the 1970s and 1980s generally describe primary failure rates of between 10 – 20%. A recent meta-analysis examining the primary failure rate of AVF estimated the pooled primary failure rate at 15.3% [9]. However, this meta-analysis included studies back to the 1960s and omitted studies published after the meta-analysis. More contemporary publications are less encouraging with reports of the primary failure rate between 20 – 54%[1]. Consistent with these findings of a high early failure rate, 50% of new patients commence haemodialysis in Australia and New Zealand with a CVC, due to a failed or inadequate AVF[10]. The higher rate of primary failure in the more recent era may reflect changing patient factors – such as older patients and a higher prevalence of diabetes.

Primary failure usually occurs as a result of one of two processes; 1) thrombosis, which usually occurs within weeks of the procedure; 2) inadequate size of the artery or maturation of the vein[8]. Strategies to reduce primary failure rates may therefore include pre-operative identification of unsuitable anatomy by the use of ultrasound, improved surgical technique and pharmacological interventions designed to prevent vessel occlusion (thrombosis).

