### Statistical Considerations

#### Sample size calculation for the primary outcome

The event rate for the primary outcome (failure of primary patency) is estimated to be 25% at three months in the control group. If a 30% relative risk reduction is achievable with either aspirin or omega-3 fatty acids, then with 80% power and a significance level of 5%, 1200 study subjects will be required (300 receiving double placebo, 300 active aspirin and placebo omega-3 fatty acids, 300 active omega-3 fatty acids and placebo aspirin, and 300 both active aspirin and active omega-3 fatty acids in a factorial design). This allows for 5% drop-in from placebo to active treatment (either aspirin or omega-3 fatty acids), 5% drop-out from study treatment (to no treatment – assumed equivalent to placebo), and 5% loss to follow-up. This is equivalent to an observed relative risk reduction of 24%. Without adjustment for compliance, the study size needed would have been 932 subjects.

The study is not adequately powered to detect a clinically important difference between the combination of aspirin and omega-3 fatty acids and either treatment alone, but preliminary data on the combination will be obtained. The event rate of the primary outcome, primary failure, is based on review of all papers published in this area. The effect size, a 30% reduction, is based on the smallest size of the effect the proposing clinicians believe would lead to a change in practice (incorporation of intervention) should the trial prove the intervention is efficacious.

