#### Sample size calculation for the secondary outcome

Sample size is estimated for the secondary outcome (failure of patency at 6 months) under assumptions of additive or multiplicative effects for each of 3 placebo rates. The calculation below is based on the following assumptions: 5% loss to follow up, 15% drop-in and 5% drop-out. The baseline failure rate of patency at 6 months is (40%, 50% and 60%) in the placebo group, the use of either aspirin or omega-3 fatty acids alone results in a relative risk reduction (RRR) of 25%, i.e. the failure rate becomes respectively 30%, 37.5% and 45% for a patient taking only one drug.

The sample size calculation is based on a marginal analysis (Z-test) with two-sided α = 0.05, power β = 90%. Table 2 presents required sample sizes under additive model (bold) and under multiplicative model

**Table 2 T2:** The sample sizes required under the additive and multiplicative models for the secondary outcome – functional patency

	Total sample size			
	
	Additive model		Multiplicative model	
	
Patency failure rate at 6 months for placebo group	unadjusted	adjusted	unadjusted	adjusted
40%	**874**	**1455**	1156	1812
50%	**620**	**1034**	820	1297
60%	**452**	**752**	596	941

(Unadjusted and adjusted refer to the calculations of sample size without and with adjustment for loss to follow-up (5%), drop-in (15%) and drop-out (5%))

A recently published comparable trial in the United States [16] experienced a placebo rate of 60% for failure of patency at 6 months. We are confident that a sample size based on a placebo rate of at least 50% is a realistic estimate and that the sample of 1,200 recruited for the primary outcome will generally be adequate for the secondary outcome whether the effect is additive or multiplicative.

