## Discussion

This multicentre Australian and New Zealand study has been designed to determine whether the outcome of surgery to create AVF can be improved by the use of aspirin and/or omega-3 fatty acids. Vascular access failure is a significant problem for patients receiving dialysis because it increases their risk of infection, hospitalisation and death. The economic costs of the increased hospitalisations arising from inadequate or artificial vascular access are considerable. Effective therapies to prevent failure of primary AVF are therefore warranted. The therapies nominated in the FAVOURED study are widely available and inexpensive.

It is an appropriate time to study the effects of anti-platelet agents in the prevention of AVF thrombosis. The number of patients requiring dialysis is growing and contemporary studies of the natural history of vascular access outcomes show an increase in the incidence of primary failure, which is most likely related to an increasing prevalence of older patients with comorbidities such as diabetes. At the time of inception of the FAVOURED study, there were no adequately powered studies examining the efficacy of anti-platelet agents in the prevention of AVF thrombosis. Subsequent to FAVOURED being launched in Australia and New Zealand, a US group has published a placebo-controlled parallel arm study examining the prevention of early thrombosis in AVFs using Clopidogrel (an antiplatelet agent) with study treatment commencing one day post surgery with a primary outcome of patency at 6 weeks [16]. There was a 12.2% thrombosis rate in the Clopidogrel arm vs. 19.5% in the control arm: RR of 0.63 (0.46–0.97) p = 0.018, adjusted for interim analyses. Suitability of the AVF for dialysis failed in 63% of the clopidogrel group and in 60% of the placebo group (61% overall). There were no differences in adverse events and, surprisingly, bleeding events were very low in both trial arms. The conclusions drawn by the investigators were that although Clopidogrel is effective in safely preventing primary AVF thrombosis, it was ineffective at increasing functional patency and therefore cannot be recommended.

The implications this trial for the FAVOURED Study include the following:

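### The statement that 1,200 patients suffice for 6-month functional patency depends on each drug preventing more failures than the primary sizing plans; at the planned 7.5-point gain, power is about 49-58%

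*Protocol article*

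**What the plan says.** All references are to the Protocol article.

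- **Sample size calculation for the primary outcome.** The failure rate is "estimated to be 25% at three months in the control group". The planned effect is conditional: "If a 30% relative risk reduction is achievable with either aspirin or omega-3 fatty acids". The choice of 30% "is based on the smallest size of the effect the proposing clinicians believe would lead to a change in practice".
- **Sample size calculation for the secondary outcome.** With placebo failure rates of 40%, 50% and 60% at 6 months, "the use of either aspirin or omega-3 fatty acids alone results in a relative risk reduction (RRR) of 25" per cent. The calculation uses 90% power, 5% loss, 15% drop-in and 5% drop-out. Table 2 gives adjusted totals of 1455/1034/752 (additive) and 1812/1297/941 (multiplicative). The text then takes a placebo rate of at least 50% as realistic and concludes that "the sample of 1,200 recruited for the primary outcome will generally be adequate for the secondary outcome whether the effect is additive or multiplicative".
- **Discussion.** On the clopidogrel trial: "There was a 12.2% thrombosis rate in the Clopidogrel arm vs. 19.5% in the control arm". Fistulas were unsuitable for dialysis in 63% of the clopidogrel group and 60% of the placebo group. The Abstract sums this up as "clopidogrel is effective in safely preventing primary AVF thrombosis, but ineffective at increasing functional patency". The Discussion adds that omega-3 fatty acids may help maturation, and that functional patency has become more important in view of that trial.

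**The concern.** The two sizing paragraphs use effects of different absolute size for the same drugs, which are taken for three months only. The primary paragraph says where its 30% comes from. The secondary paragraph states no basis for its 25%, and it does not say that this figure needs 2.5, 5 or 7.5 fewer failures per 100 beyond the planned patency gain. It takes support for its placebo rate from the clopidogrel trial, but does not mention that a 7.3-point fall in thrombosis there brought no functional gain.

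The adequacy sentence is what readers will rely on. It is not made conditional on the effect size, and it covers both models although Table 2 does not support 90% power under both at 50%. If the functional comparison turns out non-significant, a statement that the sample was adequate invites more weight on that result than the sizing can bear.

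**Working it through.** **Inputs.** Primary sizing: 25% control failure and a 30% reduction. Secondary sizing: placebo rate p = 40/50/60%, relative reduction r = 25%, two-sided 5%, 90% power, 5% loss, 15% drop-in, 5% drop-out. Equal allocation of 1,200 gives 600 per margin, or 600 × 0.95 = 570 evaluable.

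**1. The two planned gains.** Primary: 25% × 0.30 = 7.5 points. (A standard two-proportion calculation for 25% v 17.5% at 80% power gives 932 in total, as the article states.)

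| Placebo failure at 6 months | Gain at 25% reduction | Beyond 7.5 |
|---|---|---|
| 40% | 10 | 2.5 |
| 50% | 12.5 | 5 |
| 60% | 15 | 7.5 |

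**2. Reproducing Table 2.** Let c, s and b be the failure rates on neither drug, one drug and both drugs. The margins compared are A = (c + s)/2 and B = (s + b)/2, with b = 2s − c (additive) or b = s²/c (multiplicative). The number per margin is (1.960 + 1.282)² × [A(1−A) + B(1−B)] / (A−B)², where (1.960 + 1.282)² is 10.507 before rounding.

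Unadjusted, 50% additive: c, s, b = 0.50, 0.375, 0.25, so A = 0.4375 and B = 0.3125. Then 10.507 × 0.4609 / 0.125² = 310 per margin, total 620, as printed. All six unadjusted totals match.

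For the adjusted totals, set c = p(1 − 0.15r) and s = p(1 − 0.95r), and divide the total by 0.95. At 50% additive: c, s, b = 0.48125, 0.38125, 0.28125, so A = 0.43125 and B = 0.33125. Then 10.507 × 0.4668 / 0.10² = 490.5, rounded up to 491; 982 / 0.95 = 1034, as printed. The other results are 1455 and 752 (additive) and 1829, 1297 and 941 (multiplicative). Only the printed 1812 at 40% multiplicative differs, by about 1%.

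**3. Power of 1,200.** Power = Φ{(A−B) / √([A(1−A) + B(1−B)]/570) − 1.96}.

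- 25% reduction, 50% multiplicative: A = 0.43125, B = 0.34164, standard error 0.0287, ratio 3.12, power 88%.
- 7.5 points, 50% additive: r = 0.075/0.50 = 0.15; A = 0.45875, B = 0.39875, standard error 0.0293, ratio 2.05, power 54%.

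| Single-drug effect | Model | 40% | 50% | 60% |
|---|---|---|---|---|
| 25% reduction | additive | 84% | 94% | 98% |
| 25% reduction | multiplicative | 75% | 88% | 96% |
| 7.5 points | additive | 58% | 54% | 53% |
| 7.5 points | multiplicative | 51% | 49% | 49% |

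**4. Sensitivity at 7.5 points.** With the primary sizing's 5% drop-in in place of 15%, power is 57-68%. With no loss or non-compliance at all it is 68-79%. Applying the dilution to the margins rather than the cells gives 58/54/53% and 50/47/48%.

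**5. Gain needed for 90% power.** Solving the same formula for the single-drug gain, with 15% drop-in and 1,200 patients, gives about 12 points (additive) and 13 points (multiplicative) at placebo rates of 50% and 60%. That is roughly 4 to 6 points beyond the planned patency gain. At 50% multiplicative, 13 points exceeds the assumed 12.5, which is why Table 2 asks for 1,297.

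**The case against.** The tempting stronger reading is that 7.5 points is the most either drug can achieve, so that the true functional power is about 50%. The article does not support that.

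- The 30% is described as the smallest effect worth acting on. That is not a ceiling.
- Functional failure is a different endpoint. It includes failure to mature and losses between 3 and 6 months, and the Discussion suggests a maturation benefit for omega-3.
- The Background reports larger falls in thrombosis: 24% to 4% with aspirin in one small trial and 25% to 12% in pooled ticlopidine data, beside smaller or null results. If a 13-point gain carried over in full to function, 1,200 patients would have about 90-98% power.
- The clopidogrel trial tested another drug, started after surgery.
- The article says only that the sample is generally adequate, and ties this to a placebo rate of at least 50%. Table 2 openly shows totals above 1,200.
- The 49-58% joins the primary effect to the secondary sizing's heavier drop-in.
- A basis for the 25% may stand in the full protocol, which this article condenses.

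All of this limits the claim, and the missing basis is not a finding by itself. It does not rescue the adequacy sentence. The 25% is credited to either drug alone, while the Discussion's maturation argument concerns omega-3 only. Power stays below 70% at 7.5 points with the lighter drop-in. The functional definition also does not count interventions as failure, so some fistulas saved on the primary definition might have been usable anyway. Hence 7.5 points is not a deliberately pessimistic choice.

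**Conclusion.** The point holds in conditional form. The secondary sizing is arithmetically sound for the effect it assumes, apart from a trivial difference in one cell. What does not hold as written is the adequacy sentence. At the assumed 25% reduction, 1,200 patients reach 90% power at placebo rates of 50% and 60% under the additive model, but only at 60% under the multiplicative one; at 50% multiplicative, power is 88%. If the functional gain equals the planned patency gain of 7.5 points, power is 53-58% (additive) or 49-51% (multiplicative), and 57-68% with 5% drop-in. The lower figures rest on the assumption that the functional gain goes no further than the planned gain in 3-month patency. The article neither states nor excludes this. The matter concerns a secondary outcome and leaves the primary sizing untouched.

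**What to change.** In the section on sample size for the secondary outcome:

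1. Keep the 25% reduction as one scenario, and state its basis if there is one.
2. Add the power of 1,200 patients at a 7.5-point functional gain, under both models and with the drop-in rate named.
3. Replace the adequacy sentence with a conditional one. For example: on the premise that each drug achieves the full 25% reduction, 1,200 patients give at least 90% power at placebo failure rates of 50% or 60% if effects are additive, and at 60% if they are multiplicative. At these rates that reduction requires 5 to 7.5 points beyond the planned gain in 3-month patency. If the functional gain is no larger than the planned patency gain, power is about 50-60%.

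The cost is one rewritten paragraph and a less favourable stated power for the secondary outcome. The number of patients, the design and the tests do not change.

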**Trial Registration:**

Australia & New Zealand Clinical Trials Register (ACTRN12607000569404).

## Background

The incidence and prevalence of severe chronic kidney disease (CKD) is increasing due to ageing of the population and co-morbid conditions such as diabetes. Haemodialysis is the chosen renal replacement therapy for 70% of patients with end-stage kidney disease (ESKD) in Australia. However, effective haemodialysis is critically dependent upon obtaining and maintaining repeated access to the circulation. Delivering the required blood flow (>300 ml/minute) necessary for haemodialysis has long been referred to as the "Achilles' heel" of dialysis. Vascular access options include native arterio-venous fistula (AVF), synthetic arterio-venous graft (AVG) or central venous catheter (CVC). AVF is universally acknowledged as the optimal access option with the best long-term patency, lowest cost and lowest infection rate [1-3] and is the most prevalent access used in Australasia (75%)[4]. Because vascular access related surgical procedures and complications of vascular access represent a high proportion of all admissions in the ESKD population and are a major economic burden for health care providers[5], various international initiatives have made this a focus of quality care improvements[6].

Several studies confirm the risk of all cause death with artificial vascular access devices, compared with AVF as the reference group, is around 1.5 for AVG and 3 for CVC, with similar rates for infectious mortality [2,3,7]. The complications associated with AVG and CVC use are sepsis, especially staphylococcal, vascular malfunction (thrombosis) and death. The increased risk of death is directly attributable to sepsis and the need for interventions to restore patency which in themselves enhance the risk of infection. Furthermore, in comparison with AVF, CVC and AVG have a significantly increased frequency of interventions to maintain patency (assisted patency).

Therefore, while the clinical imperative is to establish AVF in as many patients as possible, primary failure because of early thrombosis and failure of maturation are the major impediments to clinical success[8]. Reports in the literature from the 1970s and 1980s generally describe primary failure rates of between 10 – 20%. A recent meta-analysis examining the primary failure rate of AVF estimated the pooled primary failure rate at 15.3% [9]. However, this meta-analysis included studies back to the 1960s and omitted studies published after the meta-analysis. More contemporary publications are less encouraging with reports of the primary failure rate between 20 – 54%[1]. Consistent with these findings of a high early failure rate, 50% of new patients commence haemodialysis in Australia and New Zealand with a CVC, due to a failed or inadequate AVF[10]. The higher rate of primary failure in the more recent era may reflect changing patient factors – such as older patients and a higher prevalence of diabetes.

Primary failure usually occurs as a result of one of two processes; 1) thrombosis, which usually occurs within weeks of the procedure; 2) inadequate size of the artery or maturation of the vein[8]. Strategies to reduce primary failure rates may therefore include pre-operative identification of unsuitable anatomy by the use of ultrasound, improved surgical technique and pharmacological interventions designed to prevent vessel occlusion (thrombosis).

Early thrombosis is defined as thrombosis within the first 30 days post-operatively[11]. There have been a number of small trials evaluating pharmacological agents aimed at reducing the early thrombosis rate. These trials utilised the anti-platelet agents, aspirin, sulphinpyrazone and ticlopidine and varied in size from as few as 5 patients up to 261 patients. Andrassey et al (n = 92) compared patients given aspirin 500 mg/day for 4 weeks with placebo: the thrombosis rate in the aspirin group was 4% compared with the control group of 24%, OR 0.15 (0.03, 0.73)[12]. Another study [13] with a smaller sample size (n = 68), did not demonstrate a benefit from aspirin. In a study using ticlopidine [14], fistula thrombosis rates for the ticlopidine versus placebo groups were 12% versus 19% (p = 0.10) respectively. Studies using sulphinpyrazone showed variable results, but were underpowered with the largest study enrolling only 36 patients[15]. Pooled data for ticlopidine suggests a reduction in thrombosis rate from 25% to 12% (p < 0.001)[14]. Thus although there is some data to suggest that anti-platelet agents may increase the primary patency of AVF, the limited evidence base and the uncertainty regarding the choice of agent has not supported the widespread use of anti-platelet agents in the prevention of AVF thrombosis. There is a strong clinical need to conduct an adequately powered clinical trial to address the important question of efficacy of anti-platelet therapy in the prevention of early thrombosis of AVF. Since the inception and launch of the FAVOURED study, a US study has been published examining the effect of anti-platelet agent clopidogrel on early AVF thrombosis[16]. We have addressed the findings of this study and their implications for FAVOURED under Discussion below.

Two anti-platelet agents have been chosen to explore their prevention of early thrombosis in AVFs, low dose aspirin and omega-3 fatty acids. Aspirin has been chosen as it has well-established anti-platelet effects, a suggestion of efficacy in the limited studies to date and because it is both inexpensive and an agent familiar to clinicians. Its use as an anti-platelet agent is well established in clinical practice for other purposes relating to thrombosis prevention particularly in patients with established cardiovascular disease. Aspirin's anti-platelet effect is mediated by the inhibition the platelet enzyme cyclo-oxygenase (COX) resulting in blockade of the synthesis of the pro-aggregatory vasoconstrictor, thromboxane A2 (TxA2).

Omega-3 fatty acids have a number of biological effects, which make them an attractive agent for the prevention of vascular access thrombosis. These include the inhibition of platelet aggregation, anti-inflammatory effects and anti-proliferative actions. Omega-3 fatty acids and aspirin both affect the balance between the pro-aggregatory and vasoconstrictor effects of TxA2 and the anti-aggregatory and vasodilator effects of prostacyclin (PGI2) but the mechanism of their effect is different. Omega-3 fatty acids have a weaker inhibitory effect on TxA2 level, their effect mediated by reducing the availability of arachidonic acid (AA), a precursor of TxA2. In addition, omega-3 fatty acids leads to an increase in PGI3 formation (anti-aggregatory and vasodilatation effects equipotent to PGI2)[17]. The anti-inflammatory effect of omega-3 fatty acids is mediated via a reduction in leukotriene and cytokine production. Theoretically, a combination of aspirin and omega-3 fatty acids should result in a more favourable effect on platelet aggregation than either agent used alone.

One study has examined the effects of low-dose aspirin in combination with omega-3 fatty acids on whole blood eicosanoid production[17]. This study demonstrated an *additive *effect of the combination on TxA2 (40% with aspirin alone vs. 62% with the combination) and a smaller reduction in the concentrations of PGI2 and PGI3 compared with aspirin alone. There has only been one study exploring the efficacy of omega-3 fatty acids in the prevention of vascular access thrombosis. This study involved the use of omega-3 fatty acids as a single agent and only explored its use in AVG, not AVF. Importantly, the study demonstrated a substantial reduction in thrombosis at 1 year in patients with AVG[18]. There are other effects of omega-3 fatty acids, which may be particularly beneficial in patients with CKD. Omega-3 fatty acids has been shown to result in an improvement in lipid profile [18-20], to reduce BP and heart rate[21], and to attenuate inflammatory responses [22] and oxidative stress[23]. Other postulated but as yet unproven benefits in the CKD population include a reduction in inflammatory response, cardiovascular mortality and a reduction in uraemic pruritis[24].

The relationship between aspirin use and bleeding is a potential concern for clinicians in patients with CKD. Even in the general population, the use of a chronic low dose of aspirin doubles the risk of serious gastrointestinal bleeding [25] and the theoretical risk may be higher in patients with CKD because of the presence of uraemic induced impairment of haemostasis. There have been published studies[26,27], showing a significant elevation in bleeding times in patients on haemodialysis treatments administered a single dose of aspirin, but surprisingly little evidence-based clinical trial data in this population. This has more recently been explored in the UK-HARP-I study. In this factorial design study involving simvastatin and aspirin as active therapies, allocation to the aspirin group was not associated with an excess of major bleeds (2% in patients on aspirin vs. 3% in patients not on aspirin), but there was a three-fold increase in minor bleeding[28]. Importantly though, in this study, patients received aspirin for 12 months, whereas our study has a much shorter period on therapy of 3 months. In addition, patients on dialysis undergoing renal transplantation have successfully received pre-operative aspirin for the prevention of graft thrombosis without an increased risk of major bleeding [29,30].

Omega-3 fatty acids appear to be well tolerated, even in high doses, with gastrointestinal complaints particularly nausea, vomiting, diarrhoea and non-specific discomfort being the most often reported. In studies looking at the effect of omega-3 fatty acids on bleeding time it has not been found to be significantly prolonged [31]. In studies that have been done thus far in the CKD cohort, there have been no clear effects demonstrated in relation to platelet aggregation and bleeding times. There has only been one report of a serious bleeding event in a single patient in an uncontrolled study[32]. Furthermore, it has been reported that administration of omega-3 fatty acids can protect the gastric mucosa against aspirin-induced injury, the postulated mechanism being that omega-3 fatty acids counteracts the effect of aspirin on the decrease in prostacyclin (combined effect of PGI2 and PGI3)[33]. This is supported by clinical data suggesting that omega-3 fatty acids decreases gastric erosions and ulcers caused by aspirin or alcohol[34]. Thus the combination of aspirin and omega-3 fatty acids may be expected to be additive in terms of efficacy in vascular access thrombosis, but to have a lower risk of bleeding complications than the use of aspirin alone.

We have chosen an oral route of administration for both aspirin and omega-3 fatty acids in this study. The choice of 100 mg for aspirin is based on this dose having adequate anti-platelet aggregation properties and is the dose most commonly used in patients with cardiovascular disease. A 100 mg dose is readily available. The dose of omega-3 fatty acids (4 g daily) has been shown to be well tolerated and improve cardiovascular risk factors in patients at increased risk of cardiovascular disease [35-39]. The marine derived omega-3 fatty acids (commonly known as fish oils) capsules chosen (Omacor^©^), are commercially available and provide the highest concentration of omega-3 fatty acids per gram of oil. The oral absorption of both agents is excellent and thus alternative routes of administration are not required.

The design of a factorial study is based on the hypothesis that aspirin and omega-3 fatty acids will both be effective therapies and that the combination of aspirin and omega-3 fatty acids will be additive, but not synergistic. In relation to safety concerns, although both aspirin and omega-3 fatty acids prolong bleeding time, the combination may be expected to be safer than when aspirin is used alone.
